
**Figure 2 F2:**
[figure not shown]
Example of a trial of the tablet-based bradykinesia test.

**Figure 3 F3:**
[figure not shown]
Example of two trials of the tablet-based Stroop test with congruent (left) and incongruent (right) conditions.

### Order of the tests

After the battery is exposed, and before the performance of the clinical tests can start, a number of preparations are required in order to programme the aDBS (see the Procedure section). This requirement can lead to individual differences in the time available to perform the clinical tests due to the maximum amount of intraoperative time allowed for this experiment. Therefore, the sequence in which the clinical tests are performed on each condition is initially ordered according to the approximate time it takes the patient to perform each of them, the suggested order being as follows: (1) tablet-based tapping test, (2) subMDS-UPDRS, (3) Speech and Intelligibility Test (SIT), (4) tablet-based version of the Stroop test. If during the course of each individual experiment it is considered that the time will not be sufficient for a patient to complete the full protocol, only the first test(s) could be selected to be performed in order to ensure that at least one of the tests will be completed for each of the three conditions.

### Sample size

According to previous studies,^35^ a difference of approximately four points in the total motor UPDRS could be considered clinically significant (3.7% of the total scale). This would be roughly equivalent to a limit of 1.5 points on a 10-item UPDRS scale, which is the one used in this protocol. Based on pilot data conducted in Oxford/London on four patients,^9^ aDBS scores had an standard error of approximately two points (SD of 4). This is roughly equivalent to an SD of 1.5 points on a 10-item UPDRS scale. Using an α of 0.05, a power (1−β) of 0.8 and assuming similar variances, a sample size of 12 patients would be necessary to demonstrate that the efficacy of aDBS is not inferior to cDBS, while providing the potential benefits of facilitating programming, battery life optimisation and the potential to reduce stimulation-induced side effects. A potential extension of two patients (14 patients in total) would be pursued in order to explore the potential effects of aDBS on patients with electrodes implanted on the GPi.

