### Trial design

This protocol describes an exploratory study in which patients with PD with DBS electrodes implanted in the STN are allocated to a three-condition (no stimulation (NoStim)/cDBS/aDBS), cross-over design (figure 1). The conditions are pseudo-randomised in a 2:1:1 format, in such a way that for every two patients who start with no-stimulation, one patient will receive aDBS first and one will have cDBS first. The main reason for this proposed pseudo-randomisation is to minimise the impact that an incomplete washout effect derived from stimulation could have on the scores of NoStim condition, as this condition is the baseline for the comparison of the effect of the two stimulation modalities. In four patients, stimulation conditions will be separated by a NoStim condition to minimise the carryover effect that cDBS could have on aDBS (or vice versa). Lastly, NoStim will be the last condition in two patients in order to partially balance the effects of training or fatigue on the tasks. Additionally, pilot data could be collected from two patients in order to explore the effects of aDBS on the GPi.

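### The 80% power for 12 patients is built on the spread of aDBS scores between patients, not on the within-patient aDBS-cDBS difference, so it is not the power of this cross-over

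*Protocol article*

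**What the plan says.** The Trial design section of the protocol article describes a three-condition "cross-over design" in which each patient is tested without stimulation, on cDBS and on aDBS. The Statistical methods section compares the conditions with a linear mixed-effects model.

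The Sample size section sets a margin described as "roughly equivalent to a limit of 1.5 points on a 10-item UPDRS scale". For the variability it turns to a pilot ("Based on pilot data conducted in Oxford/London on four patients") and reports that "aDBS scores had an standard error of approximately two points (SD of 4"). It rescales this SD to 1.5 points. The calculation is then stated as: "Using an α of 0.05, a power (1−β) of 0.8 and assuming similar variances", leading to 12 patients "to demonstrate that the efficacy of aDBS is not inferior to cDBS".

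The Allocation section sets 10 patients as an initial goal, with two more possible depending on aborted experiments and the inclusion deadline.

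**The concern.** When each patient provides both scores, the comparison of aDBS with cDBS is made within patients. Its precision depends on the SD of the paired difference or, equivalently, on the SD of each condition together with the correlation between the two scores of one patient. The Sample size section gives neither the SD of the difference nor the correlation. It uses the SD of scores in one condition and assumes equal variances, which are the inputs of a comparison between two separate groups.

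At stake is what the 80% means. It is attached to a non-inferiority claim with a stated margin, and a reader will take it as the chance that this trial succeeds if aDBS and cDBS are equally effective. If it belongs to another design, the true chance may be higher or lower, and the article does not allow the reader to tell which.

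**Working it through.** **Inputs from the Sample size section.** Margin 1.5; SD 1.5; alpha 0.05, sidedness not stated; power 0.8; four pilot patients; stated n = 12. True difference 0 is an assumption, usual for non-inferiority.

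**What the SD is.** A standard error of 2 in four patients gives 2 × √4 = 4, the SD quoted. It is therefore the spread between patients in the aDBS condition alone. The four-point difference is given as 3.7% of the total scale, which implies 108 points. Ten items scored 0 to 4 make 40 points, and 4 × 40/108 = 1.48, rounded to 1.5.

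**Reproducing the 12.** For two independent groups, n per group = 2 × (z₁₋α + z₁₋β)² × (SD/margin)².

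- One-sided 5%: 2 × (1.645 + 0.842)² × (1.5/1.5)² = 12.37. With the unrounded SD of 1.48 it is about 12.1.
- One-sided 2.5%: 2 × (1.960 + 0.842)² = 15.70, that is 16.

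If 1.5 had been taken as the SD of the paired difference, the factor 2 drops out:

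- One-sided 5%: 6.2 by the normal formula, 8 by the exact paired t.
- One-sided 2.5%: 7.9 by the normal formula, 10 by the exact paired t.

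The stated 12 is nearest to the independent-groups result at one-sided 5%.

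**Power of the paired comparison.** With equal variances, SD of the difference = 1.5 × √(2(1 − ρ)), where ρ is the correlation between a patient's aDBS and cDBS scores. The documents give no ρ, so a range is assumed. Power is the probability that a noncentral t variable with n − 1 degrees of freedom and noncentrality 1.5 / (SD of difference/√n) exceeds the one-sided critical value.

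| Assumed ρ | SD of difference | n = 12, one-sided 5% | n = 12, one-sided 2.5% | n = 10, one-sided 5% | n = 10, one-sided 2.5% |
|---|---|---|---|---|---|
| 0 | 2.12 | 74% | 61% | 66% | 51% |
| 0.15 | 1.96 | 80% | 68% | 72% | 58% |
| 0.2 | 1.90 | 82% | 70% | 75% | 61% |
| 0.5 | 1.50 | 94% | 88% | 90% | 80% |
| 0.7 | 1.16 | 99% | 98% | 98% | 95% |

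**Break-even.** With 12 patients, 80% power requires an SD of the difference of at most 1.96 (ρ about 0.15 or more) at one-sided 5%, or at most 1.69 (ρ about 0.37 or more) at one-sided 2.5%.

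**Precision of the SD.** With four pilot patients and normal scores, the chi-square 95% interval around an SD of 1.5 runs from about 0.85 to 5.6.

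**The case against.** The strongest reply has four parts.

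- **The formula is not named.** This stands. The independent-groups reading is an inference from the closeness of 12.4 to 12 and from the equal-variance assumption; strict rounding up would give 13. It does not rescue the 80%, however. The nearest paired reading (n = 10, one-sided 2.5%) would treat the SD of one condition as the SD of a difference.
- **Treating the scores as independent is conservative.** This stands in part. Non-inferiority is one-sided by nature. If 0.05 is the one-sided level, 12 patients give at least 80% once ρ exceeds about 0.15, a low bar for two scores from the same patient on the same items in one session. A reader might infer from the 61% or 51% in the table that the trial is underpowered. The documents do not support that: those figures need both zero correlation and a one-sided level of 2.5%, and neither is stated.
- **Sidedness and formula may be in the full protocol.** Their absence from an article is not an error in itself, and the point does not rest on it. It rests on a calculation that is presented, with an SD that does not match the design presented beside it. Sidedness matters here because the corrected power cannot be stated without it.
- **The study is exploratory, and the confidence interval will be informative whatever the planned power.** The interval from the mixed model can indeed be set against the 1.5 margin after the trial. Yet the Sample size section presents 12 as the number needed to demonstrate non-inferiority, so the power attached to it should be that of the design.

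Two further arguments are tempting and should not be made. One is that proportional rescaling of the SD to ten items makes it too small; its direction depends on item variances and correlations that the documents do not give. The other is that the SD of the difference can simply be taken from the pilot; the article does not say that paired differences are available, and four patients would fix the SD poorly.

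**Conclusion.** The point holds as a mismatch between the stated power and the design. The 80% is derived from the SD of one condition and does not describe a within-patient comparison of aDBS with cDBS in 12 patients. On the plan's margin and SD, with no true difference and ρ assumed between 0 and 0.7, paired power at 12 lies between 74% and 99% at one-sided 5%, and between 61% and 98% at one-sided 2.5%.

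The direction is unknown because ρ is unknown. At one-sided 5% the stated figure is probably too low rather than too high. The finding therefore concerns the justification of the sample size and gives no reason to change the number of patients. The figures assume equal variances and normally distributed differences, with a simple paired t standing in for the mixed model.

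**What to change.** Keep 12 patients. In the Sample size section, replace the single 80% by the power of the paired comparison over a stated range of the SD of the aDBS-cDBS difference. Give it for 12 patients and for the initial goal of 10 in the Allocation section, and say which one-sided alpha level is used. The table above can serve as the basis, with a sentence stating that the correlation is assumed and that the pilot SD rests on four patients.

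The cost is one rewritten paragraph, with no extra patients, tests or procedures. The stated power becomes a range whose lower end may fall below 80%.

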### Recruitment

Patients who are scheduled for a battery replacement at the University Medical Centre Groningen are contacted by telephone 2 weeks before their hospital admission to be informed about the study. Complementary written information is sent by mail to patients who show an interest in participating in the study. At the time of hospital admission, each patient is personally approached by one of the members of the research team, if they meet all of the inclusion criteria and none of the exclusion criteria. Patients who decide to participate in the study will then be given the opportunity to ask further questions and invited to sign the consent form.

### Methods: assignment of interventions

#### Allocation

The ultimate goal of the allocation procedure is to have a pseudo-randomisation in which all the possible combinations of the block design are covered (ie, 2:1:1, see the Trial design section, figure 1). For that reason, patients will be sequentially allocated to each possible pseudo-randomisation scenario until 14 patients are allocated. Only successful bilateral measurements will be considered in the pseudo-randomisation list. At first, a pseudo-randomisation of 3:1:1 (10 patients) will be set as the allocation goal in order to ensure that all conditions of the pseudo-randomisation could be met by mid-2019. Depending on the number of aborted experiments and the deadline for inclusion, two patients more may potentially be included to achieve the 2:1:1 pseudo-randomisation.

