### Procedure

Patients have to skip at least one medication dose and are not allowed to be under the effect of prolonged-release dopaminergic medication in order to be classified as OFF medication before surgery. Patients are brought to the operating theatre for their battery replacement procedure. After the battery is exposed, the old battery is detached from the DBS electrodes and explanted. At this moment, two temporary wires are attached to the DBS electrode extension cables and connected to a combined stimulator and amplifier (see previous section). A brief rest recording of 30–60 s is performed from each of the two bipolar montages (0–2 or 1–3) available for each hemisphere. Power spectral density estimates are obtained from each rest recording, and the bipolar contact pair (0–2 or 1–3) per hemisphere with the highest beta peak power is selected. Monopolar cDBS is then titrated using the available contact located between the selected recording contacts. The voltage for monopolar stimulation is titrated initially based on an approximation of the voltage used in clinical practice for each individual patient (independently of the montage used in clinical practice). Voltage is increased or decreased according to the presence of side effects, clinical effect and interference with LFP recordings (in practice, we have seen that voltages>3.5 V are more prone to cause interference with the recordings, and these are also rare stimulation parameters in clinical practice). Once an optimum stimulation voltage is established, the patients are assigned to each of three counterbalanced conditions in which the patient is either stimulated with aDBS or cDBS, or not stimulated, separated by washout periods of 1–3 min, according to the remaining time available. Stimulation parameters (voltage, frequency, pulse width and contact selection) remain constant for both aDBS and cDBS, differing only in the timing of stimulation delivered according to beta detection. As battery replacements are performed under local anaesthesia, we aim to limit the duration of the experiment to a maximum of 25–30 min.

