## Ethics and dissemination

### Protocol amendments

The protocol presented here is the fifth version (9 December 2018) of the original protocol prepared for this study. The second version of the protocol (15 September 2015) got the approval of the ethical committee after several modifications of the first version (22 July 2015). In version 3 (12 April 2017), an attempt was made to include patients undergoing new implantations. However, this was dropped in subsequent versions, since (a) patients undergoing new implantations were often considerably fatigued at the moment of the measurement and could not perform all the tasks; (b) differences in total intraoperative time between new implantations and battery replacements meant that the time available for the measurement was considerably less during new implantations; (c) the stereotactic frame slightly restricted the visual field of the patients in new implantations. Version 4 (7 September 2017) and version 5 were meant to increase the total number of patients to be included, as several failed or incomplete measurements took place during the initial inclusions.

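### Sequences are filled in turn rather than drawn at random, and an undefined success criterion that can be judged after testing has begun decides which sessions keep their slot

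*Protocol article*

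**What the plan says.** Under Allocation, the protocol article states that "patients will be sequentially allocated to each possible pseudo-randomisation scenario until 14 patients are allocated". The next rule is that "Only successful bilateral measurements will be considered in the pseudo-randomisation list". No random element, concealment or definition of success is given. The figure with the pseudo-randomisation block is not shown in the copy reviewed.

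The same section ties later enrolment to failures. At first "a pseudo-randomisation of 3:1:1 (10 patients) will be set as the allocation goal", and then: "Depending on the number of aborted experiments and the deadline for inclusion, two patients more may potentially be included to achieve the 2:1:1 pseudo-randomisation". Under Trial design the target is stated as "The conditions are pseudo-randomised in a 2:1:1 format".

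Under Procedure, assignment follows contact selection and titration: "Once an optimum stimulation voltage is established, the patients are assigned to each of three counterbalanced conditions". Under Protocol amendments, versions 4 and 5 are explained by the fact that "several failed or incomplete measurements took place during the initial inclusions". The number is not given.

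**The concern.** Two features of the allocation rule matter.

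**Predictability.** If scenarios are worked through in turn, the team can foresee the next patient's sequence. Sequence is then tied to calendar time, and so to growing experience with the device, in a study of only 10 to 12 STN patients.

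**Selection after assignment.** A slot counts as filled only when its session is judged successful, and that can be known only during or after the session. A session that fails once a condition has started is replaced by a later patient. The study aims to show that aDBS is not inferior to cDBS, and aDBS depends on working beta detection. A session lost because detection or triggering failed carries information about aDBS. If the completed sessions alone answered the question, the estimate would probably move towards non-inferiority. Comparing each patient with himself or herself gives no protection, because what would be selected is that within-patient difference.

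**Working it through.** **1. The plan's own figure.** Inputs from Sample size: margin 1.5 points, SD 1.5 points, α 0.05 (sidedness not stated), power 0.80. With a true difference of zero and one-sided α 0.05:

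n = 2 × (1.645 + 0.842)² × (1.5/1.5)² = 12.4, rounded up to 13.

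This agrees closely with the stated 12. It corresponds to a paired comparison in which the SD of the difference is √2 × 1.5 = 2.12. One-sided α 0.025 would give 16, so one-sided 5% is used below. The calculation has no allowance for failed sessions: if 12 must be successes, the number started is open-ended.

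**2. Slots.**
- 3:1:1 with 10 patients: 6/2/2.
- 2:1:1 with 12 patients: 6/3/3.
- 2:1:1 with 14 patients: 7/3.5/3.5, so the ratio can apply only to the 12 STN patients.

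Going from 10 to 12 adds one aDBS-first and one cDBS-first patient. Whether those two are enrolled depends partly on how many experiments were aborted, so failures also influence the final mix of sequences.

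**3. Sessions needed.** Started sessions = 12/(1 − f). The failure rate f is not given; the assumed range is 10% to 40%. This gives 13.3, 15.0, 17.1 and 20.0 sessions at f = 10, 20, 30 and 40%.

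**4. Possible effect of selection (illustration, all inputs assumed).** Let d be a patient's aDBS-minus-cDBS score, positive when aDBS is worse, with a true mean at the 1.5-point margin. Let failure have latent correlation r with d, and analyse the first 12 successful patients. With c = Φ⁻¹(1 − f) and φ the standard normal density:

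shift in favour of aDBS = r × SD of d × φ(c)/(1 − f).

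For f = 0.2, r = 0.5 and SD 1.5: 0.5 × 1.5 × 0.280/0.8 = 0.26 points. The simulated error of a nominal one-sided 5% test, with SD of d = 1.5, is:

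| f | r = 0 | r = 0.3 (shift) | r = 0.5 (shift) |
|---|---|---|---|
| 10% | 5% | 7% (0.09) | 9% (0.15) |
| 20% | 5% | 10% (0.16) | 15% (0.26) |
| 30% | 5% | 13% (0.22) | 21% (0.37) |
| 40% | 5% | 16% (0.29) | 30% (0.48) |

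With SD of d = 2.12 the shifts are larger (0.12 to 0.68 points) and the error rates nearly the same.

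**5. A harsher illustration.** Suppose 3 of 15 started sessions fail and the aDBS deficit in them is 2 points larger. The successful-only estimate is then too small by 0.2 × 2 = 0.4 points, which is 0.4/1.5 = 27% of the margin. The standard error is 1.5/√12 = 0.433 or 1.5 × √(2/12) = 0.612. The error becomes Φ(−1.645 + 0.4/0.612) = 0.16 or Φ(−1.645 + 0.4/0.433) = 0.24. The assumption is strong: with an overall deficit of 1.5, the failed patients would have a deficit of 3.1.

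**6. What a mixed model can recover.** In step 5, suppose the failed patients have no aDBS score and the same expected cDBS and no-stimulation scores as the others. Their retained scores then say nothing about their poorer aDBS response. The model still estimates the aDBS mean of the successful patients, and the 0.4 points remain. Retention helps where both aDBS and cDBS were scored before the session failed.

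**The case against.** The best case for the plan has five parts.

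- **Allocation is not analysis.** The success rule says which sessions fill a slot. A reader might infer that failed sessions are left out of the analysis, but no section says so. Statistical methods plans a linear mixed-effects model and excludes nobody, and analysis sets may be defined in a document not shown. This stands: the defect is in the allocation rule, and exclusion from analysis is not established.
- **Failures are not hidden.** A reader might infer that they vanish from view. The Allocation section itself mentions aborted experiments, and Protocol amendments reports failed or incomplete measurements. This stands.
- **Failures may be harmless.** Externalisation, rest recordings, beta-peak selection and titration all precede the first tested condition. Failures there cannot select on the aDBS-cDBS contrast. The fatigue described under Protocol amendments concerns new implantations, since dropped. Under Order of the tests, sessions short of time lose the later tests so that one test can be completed in all conditions. This stands in part: it shows that many failures could be innocent, but the plan does not separate them from the others.
- **Foreknowledge can do little.** Everyone receives all three conditions, patients and recording raters are blinded, and tablet scoring is automated. The order in the figure cannot be checked. This limits the harm. It does not stop a team that knows the sequence from influencing who is tested next or when a session is called unsuccessful.
- **Replacement has a purpose.** Trial design puts no stimulation last in only two patients and between the stimulation conditions in four. Failed sessions could empty such small cells. This stands, and replacement may continue.

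The study is also labelled exploratory, which lowers the stakes, although Sample size is built on a non-inferiority claim.

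**Conclusion.** The point holds in a limited form. As written, the rule makes the next sequence foreseeable, ties sequence to calendar time, and lets an undefined judgement, possibly made after testing has begun, decide who is replaced. Reading *sequentially* as a fixed order is natural, but it cannot be confirmed without the figure.

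Bias towards non-inferiority is conditional. It requires that failures after assignment relate to the aDBS-cDBS difference and that the completed sessions carry the conclusion. Neither is documented. A failure during no stimulation has no determined direction for this contrast. The error rates above, including the 16% to 24% in the harsher illustration, rest wholly on assumed inputs and should not be read as the trial's error rate. If failure is unrelated to the contrast there is no inflation.

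This is a cheap improvement worth making. It does not show that the results would be invalid.

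**What to change.** 1. Draw the order of the 12 STN sequences (6/3/3) once, as a computer-generated random permutation. Assignment already follows titration under Procedure; conceal the next sequence until that moment.
2. Define *successful* in advance, including whether a session with only the first test or tests completed counts. Separate failures before the first condition, which can be replaced without harm, from failures after it.
3. Keep every patient who starts a condition in the planned mixed model, under the sequence given, using all scored conditions. Add a period term, which Statistical methods does not name. Present the complete sessions as a second analysis.
4. Report failures by condition, period and reason.
5. Add a sensitivity analysis that counts sessions in which aDBS could not be delivered as unfavourable to aDBS, because the mixed model alone cannot correct for missing aDBS scores.
6. Replacement patients may still be added to preserve the small sequence cells, alongside the patients they replace.

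The cost is a one-off random list, slightly unequal sequence counts and a little more analysis work. The period term adjusts for order effects under unequal counts but does not deal with carryover, which is why item 6 keeps the cells filled. No extra procedures are needed, and no patients beyond the replacements the plan already allows.

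### The first allocation goal of 10 patients falls short of the 12 that the power statement and sequence layout require, and the step to 12 is optional

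*Protocol article*

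**What the plan says.** Three sections of the protocol article bear on how many patients are needed and in which order they receive the conditions.

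- **Sample size.** The test conditions are given as "Using an α of 0.05, a power (1−β) of 0.8 and assuming similar variances". The non-inferiority limit is "roughly equivalent to a limit of 1.5 points on a 10-item UPDRS scale", and the variability is stated as follows: "This is roughly equivalent to an SD of 1.5 points on a 10-item UPDRS scale". The conclusion is that "a sample size of 12 patients would be necessary to demonstrate that the efficacy of aDBS is not inferior to cDBS". The section then adds: "A potential extension of two patients (14 patients in total) would be pursued in order to explore the potential effects of aDBS", meaning patients with GPi electrodes.
- **Trial design.** The ratio of NoStim-first to aDBS-first to cDBS-first is 2:1:1. Four patients have NoStim between the two stimulation conditions, to limit carryover between aDBS and cDBS. In addition, "NoStim will be the last condition in two patients in order to partially balance the effects of training or fatigue on the tasks". Up to two GPi patients are described as additional pilot data.
- **Allocation.** The section says that "patients will be sequentially allocated to each possible pseudo-randomisation scenario until 14 patients are allocated". It continues: "At first, a pseudo-randomisation of 3:1:1 (10 patients) will be set as the allocation goal", with the aim of covering all conditions by mid-2019. Two more patients may then be added to reach 2:1:1, depending on aborted experiments and the inclusion deadline. Only successful bilateral measurements count towards the list.

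**The concern.** The number called necessary in one section is optional in another. The trial could close with 10 evaluable patients, having met its first allocation goal, and still be reported against a sample size statement that says 12 were needed. The protocol gives neither the power nor the sequence layout that would apply at 10.

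The possibility is not remote. Protocol amendments reports that versions 4 and 5 raised the number of patients because several measurements had failed or were incomplete. The current version is dated December 2018, and the 10-patient goal is tied to mid-2019.

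Two things are at stake: the power of the aDBS versus cDBS non-inferiority comparison, and the safeguard against carryover between aDBS and cDBS. The second matters because the Procedure section allows washouts of only 1–3 min. Sequences not run cannot be recovered in the analysis.

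**Working it through.** **1. Reproducing the planned 12.** Inputs from Sample size: margin 1.5, SD 1.5, α 0.05 (sidedness not stated), power 0.80. The protocol gives neither a within-patient correlation nor an SD of the paired difference. Taking one-sided 5% and zero correlation (both assumptions), the SD of the difference is 1.5 × √2 = 2.12, and

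n = 2 × (1.645 + 0.842)² × (1.5/1.5)² = 12.37.

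This rounds up to 13, close enough to count as reproducing 12. One-sided 2.5% with zero correlation gives 15.70, which does not. One-sided 2.5% with an assumed correlation of 0.25 gives 11.77, which does.

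**2. Power at 10 and 12.** By the normal approximation, power = Φ(1.5 × √n / SD of difference − z), where z is 1.645 at one-sided 5%.

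- n = 12: Φ(2.449 − 1.645) = 78.9%
- n = 10: Φ(2.236 − 1.645) = 72.3%

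Results for the readings tried:

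| Assumed correlation, one-sided α | Normal, n=12 | Normal, n=10 | Paired t, n=12 | Paired t, n=10 |
|---|---|---|---|---|
| 0, 5% | 78.9% | 72.3% | 74.2% | 66.2% |
| 0.25, 2.5% | 80.7% | 73.3% | 73.1% | 63.4% |
| 0.25, 5% | 88.2% | 82.6% | 84.2% | 76.9% |
| 0.5, 5% | 96.6% | 93.5% | 94.5% | 89.8% |
| 0.5, 2.5% | 93.4% | 88.5% | 88.3% | 80.3% |

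In the first two rows, where the normal approximation comes closest to 12 patients for 80% power, stopping at 10 costs about 7 points (8 to 10 by paired t). With a correlation of 0.5, power at 10 stays between 80% and 94%.

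**3. Sequence counts.** Four NoStim-middle plus two NoStim-last make six patients who start with stimulation. At 2:1:1 these are half the total, so the other six start with NoStim and the total is 12: 6/4/2 by NoStim position (first/middle/last), and 6:3:3 by starting condition.

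At 3:1:1 in 10 patients the split is 6:2:2, which leaves only four stimulation-first patients against the six that Trial design requires. Allocation aims to cover all possible combinations. With two aDBS-first and two cDBS-first patients, covering all six orders means one NoStim-middle and one NoStim-last in each pair, hence 6/2/2 by NoStim position. Figure 1 is not available here, so this layout is derived from the text.

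- NoStim-middle patients: 4 at n = 12, 2 at n = 10.
- aDBS and cDBS back to back (NoStim first or last): (6 + 2)/12 = 67% at n = 12, and (6 + 2)/10 = 80% at n = 10.

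**4. The figure of 14.** 14 at 2:1:1 would be 7 : 3.5 : 3.5, which is not possible in whole patients. Sample size explains 14 as 12 plus 2 GPi patients, and 12 does split exactly. Allocation fills the scenarios up to 14 without saying that the GPi patients stand outside the block.

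**The case against.** The strongest defence is that the plan is staged and coherent. Allocation names 2:1:1 as the ultimate goal and 10 only as the goal at first. Going from 6/2/2 to 6/4/2 means adding one patient to each NoStim-middle order, which gives exactly the layout in Trial design. At 12 the stated size and layout are both met. It would therefore be wrong to say that they will not be delivered. What stands is that they are not guaranteed, because the second stage is optional.

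The power loss also rests on an unstated correlation, and a crossover normally has some. With enough of it, 10 patients would suffice. That is fair, but the protocol does not make the argument: it gives no correlation and calls 12 necessary. By the paired t calculation with zero correlation even 12 gives only 74%, so returning to 12 restores the plan's own basis rather than assuring 80% on every method. Trial design calls the study exploratory, yet Sample size claims a powered non-inferiority demonstration.

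At 10, aDBS-first and cDBS-first stay equal in number, so the main contrast remains balanced for which stimulation condition comes first. The mean position of NoStim barely moves, from (6×1 + 4×2 + 2×3)/12 = 1.67 to (6×1 + 2×2 + 2×3)/10 = 1.60. The cost lies in the separated sequences.

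Three stronger readings are tempting but not supported:

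- *That 14 is a rival target.* Sample size explains it as the 12 plus a GPi extension. Only the missing separation in Allocation is at fault.
- *That the NoStim-last sequences would vanish at 10.* A 6/4/0 layout would omit two of the six orders, against the stated aim of covering all combinations.
- *That sequential filling of slots biases titration.* Procedure assigns conditions after the voltage is set and holds the stimulation parameters equal for aDBS and cDBS. Nothing says that the team knows the order beforehand.

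**Conclusion.** The point holds as an inconsistency between Sample size, Trial design and Allocation. The trial can meet its first allocation goal of 10 while missing the 12 patients it calls necessary and the sequence counts it specifies.

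The sequence part rests on counting alone: 10 patients at 3:1:1 provide four stimulation-first patients where six are required. If all six orders are covered, the separated sequences are halved and back-to-back aDBS/cDBS rises from 8/12 to 8/10.

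The power part is conditional. It is about 79% at 12 against 72% at 10 (paired t: 74% against 66%), assuming one-sided 5% and zero within-patient correlation. At the same α the loss is smaller with positive correlation, and 10 could then be adequate.

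The GPi part is a gap in Allocation: as written, the text leaves open whether pilot patients take places in the STN block.

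**What to change.** Reconcile Trial design, Sample size and Allocation in one of two ways:

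1. Set 12 evaluable STN patients in the 6/4/2 layout as the single target, and remove the wording that makes the last two optional; or
2. If stopping at 10 is acceptable, say so in Sample size. State the power at 10 with its assumptions (sidedness and within-patient correlation), and give the sequence layout at 10 in Trial design.

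In either case, put the up to two GPi patients on a separate list, outside the STN block and the STN non-inferiority analysis, so that 14 reads everywhere as 12 plus 2.

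The cost is an amendment paragraph and one allocation list, with no patients beyond the 12 already stated. The downside is a less favourable power figure if inclusion stops at 10. The choice should be made before inclusion closes.
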